## Abstract

**Introduction:**

Catheter use is associated with many complications and is an iatrogenic source of morbidity and mortality in intensive care units (ICU). The catheter being studied (Certofix Protect) was developed to reduce the risk of catheter related infections. This clinical trial will compare the safety and efficiency of Certofix Protect with that of an ordinary Certofix catheter.

**Methods and analysis:**

In this multicentre trial, we will randomly assigned dual lumen central venous catheterisation (≥5 ds) in patients in the adult ICU to the antimicrobial central venous catheter (CVC) group or the ordinary CVC group. We plan to recruit 12–16 medical centres in China. Our main objective is to assess the effectiveness of antimicrobial CVCs in reducing catheter related bloodstream infection (CRBSI), all cause mortality, catheter colonisation, catheter related thrombosis and other catheter related complications. The primary outcome is the incidence of CRBSI.

**Ethics and dissemination:**

The ethics committee of West China Hospital of Sichuan University has granted ethics approval for this study (27 January 2015). The results will be published in peer reviewed journals and presented at conferences.

**Trial registration number:**

NCT02645682.

Strengths and limitations of this studyWe will include large samples from 12–16 medical centres across different provinces which will make the results a good representation of Chinese ICU patients.Our follow-up time is not fixed. Patients will be followed until discharged from hospital. We may be unable to observe the effect of central venous catheterisation on long term quality of life.Different puncture skills may influence the risk of mechanical and infectious complications. Our study will not collect data on this issue.

## Introduction

Over the past 30 years, central venous catheters (CVC) have been an essential part of the management of critically and chronically ill patients. However, CVCs are associated with a variety of complications, including mechanical injury, infection, and thrombosis, and can lead to increased hospital costs and longer hospital stays and mortality.^1–3^

Catheter related bloodstream infection (CRBSI) is one of the most common, lethal and costly complications in patients with indwelling CVCs.^4^ Studies have reported that CVCs coated or impregnated with antimicrobial agents reduced CRBSI and catheter colonisation, but did not reduce systemic infections and all cause mortality.^5–13^ Catheter related thrombosis (CRT) is another common complication of long term indwelling CVCs.^14–18^ CRT can cause complications such as pulmonary embolism and infection. Critically ill patients with CRBSI are more likely to get CRT.^19 20^ Although many studies on antimicrobial catheters, CRT and the relationship between them have been conducted, research in China is limited.

We conducted this multicentre study to assess the effectiveness of Certofix Protect (see online supplementary appendix–study catheter) at reducing CRBSI, catheter colonisation and CRT in critically ill Chinese adult patients. We will also try to establish the relationship between catheter related infections and CRT.

10.1136/bmjopen-2017-016564.supp1Supplementary file 1

## Methods

### Study design

This is a prospective, multicentre, parallel group, controlled, randomised clinical trial conducted at 12–16 hospital centres in China from April 2016 to December 2017. The ethics committee of West China Hospital of Sichuan University has granted ethics approval for this study (27 January 2015).

### Eligibility criteria

Inclusion criteria: (1) adult patients (>18 years) admitted to an intensive care unit; (2) dual lumen CVC; (3) patients expected to require indwelling catheterisation for at least 5 days; and (4) patients who provide signed informed consent. Peripherally inserted venous catheters, peripherally inserted arterial catheters (including FloTrac), femoral arterial catheters (including PiCCO), haemodialysis, pulmonary arterial catheters, and peripherally inserted central catheters can be used in the study. All other catheters are not permitted.

Exclusion criteria: (1) pregnant women or women who have recently given birth; (2) patients with malignant diseases and unlikely to survive for the next 28 days in the opinion of the intensive care unit consultant; (3) patients with suspected catheter related infections; (4) patients receiving an initial study catheter through guidewire exchange; (5) patients hospitalised for severe burn injuries; (6) patients with, in the opinion of the doctor, a situation that is not suitable for indwelling placement, including allergy to the catheter material, confirmed deep vein thrombosis, chronic inflammatory skin disorders at the catheter insertion site, coagulation dysfunction (such as antithrombotic prophylaxis), and abnormal anatomical structure (enlargement of the thyroid glands, cervical tumours, severe pneumonectasis, or post-surgical changes in the insertion site); (7) patients who have been enrolled in the study before (during hospitalisation); and (8) patients enrolled in another investigative trial in the past 3 months.

The intervention group is those patients that undergo catheterisation with Certofix Protect. The control group is patients that undergo catheterisation with Certofix. Patients are prospectively followed from the day of CVC insertion for at least 5 days or until CVC removal, whichever comes first. Table 1 shows a schedule for participant enrolment, interventions, assessments and visits. During treatment, local investigators are required to collect data and samples from patients and arrange tests. All notices are provided in the online supplementary appendix.

**Table 1 T1:** Time of visit and data collection

	Enrolment	Allocation	Post allocation	Closeout
Informed consent	×			
Inclusion/exclusion criteria	×			
Randomisation	×			
Medical history and physical examination	×			
Temperature		×	×	
Insertion		×		
Blood test		×	×	
Blood culture			×	
Culture of CVC			×	
Vein ultrasound		×	×	
AE/SAE	×	×	×	×
Treatment/drug combination	×	×	×	×

AE, adverse effect; CVC, central venous catheter; SAE, serious adverse effect.

### Study endpoints

The primary endpoint is CRBSI. CRBSI^21^ is defined as CVC tip colonisation, using a quantitative or semi-quantitative method, and at least one peripheral blood culture positive (two separate peripheral blood cultures in the case of skin contaminants) for the same microorganism or at different times for positivity (>120 min from central and peripheral blood cultures). Clinicians should ensure the infection cannot be from another identifiable source. Each suspected case should be discussed with the chief doctor of the medical group and presented to an independent data safety monitoring committee. Secondary endpoints are catheter colonisation; attack rate of CRT (insertion side or contralateral side); morbidity from CRT (insertion side or contralateral side); and hospital mortality. Catheter colonisation^21^ is defined as any positive semi-quantitative culture of a distal catheter segment using the roll plate method (Maki method). Detailed descriptions of how and when outcome measures are defined can be found in the online supplementary appendix–supplemental method.

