### Randomisation

Each research centre will receive sequentially numbered containers used to implement the random allocation sequence, and the treatment allocation group will be hidden beyond the coated card. To ensure that patients are randomly assigned at a 1:1 ratio at each study centre, the randomised cards will be protected using a block design (each block includes four random allocation sequences). For a patient who meets the required criteria, the local investigator opens a randomised card that records the screening number and treatment allocation group. Then, the physician in charge of the patient will obtain the correct study catheter and complete catheterisation. Hence treatment allocation will be concealed.

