### Quality control

Quality control is defined as ‘a part of quality management focused on fulfilling quality requirements’ (ISO 9000:2005, clause 3.2.10). This approach places an emphasis on three aspects: (1) elements: such as controls, job management, defined and well managed processes,^23^ performance and integrity criteria, and identification of records; (2) competence: such as knowledge, skills, experience and qualifications; and (3) soft resources: such as personnel, integrity, confidence, organisational culture, motivation, team spirit and quality relationships. In study management, quality control requires that the project manager and the team inspect the work to ensure its alignment with the project scope.^24^

An independent data safety monitoring committee (comprising experts from each centre who are not investigators) has been established to oversee the safety of the trial participants and may suggest terminating the study when the outcome of the interim analysis reaches the determined threshold. Principal investigators will centralise all of the data monthly and send a newsletter (the newsletter will report inclusion cases and completed cases in each centre) to participating centres to promote data quality and the process of the trial.

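### The source-exclusion judgement and case referral for CRBSI rest with clinicians who know the catheter, and no masked classification of all culture-positive patients is stated

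*Protocol article*

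**What the plan says.** **Definition.** The Study endpoints section of the protocol article requires "CVC tip colonisation, using a quantitative or semi-quantitative method, and at least one peripheral blood culture positive" for the same organism (two separate cultures for skin contaminants), or a difference in time to positivity of more than 120 minutes between central and peripheral cultures. It then adds a judgement: "Clinicians should ensure the infection cannot be from another identifiable source".

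**Route of review.** The next sentence reads "Each suspected case should be discussed with the chief doctor of the medical group and presented to an independent data safety monitoring committee". The article does not say who has the final word. It leaves detail on how and when outcomes are defined to a supplement that is not shown.

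**Knowledge of the arm.** Under Randomisation, "the local investigator opens a randomised card that records the screening number and treatment allocation group", and then "the physician in charge of the patient will obtain the correct study catheter and complete catheterisation". The section ends "Hence treatment allocation will be concealed". That is a statement about allocation concealment. The article says nothing about masking clinicians or outcome assessors.

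**Committee.** Quality control describes the committee as "comprising experts from each centre who are not investigators" and says it "may suggest terminating the study when the outcome of the interim analysis reaches the determined threshold".

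**Cultures.** Table 1 lists blood culture and catheter culture as post-allocation items. Data collection and inspection lists peripheral blood, catheter blood and tip cultures with the catheter removal data. Neither place restricts them to suspected cases.

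**The concern.** Critically ill patients often have more than one possible source of infection, so the rule that no other source be identifiable can move a culture-positive patient into or out of the endpoint. The person applying that rule, and deciding whether to raise the case, can be expected to know whether the catheter is the antimicrobial one. If that knowledge makes another source seem more likely, antimicrobial-arm cases are lost at a higher rate than control-arm cases. A larger sample would not remove such a bias.

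The article's review step does not clearly guard against this. Its trigger is suspicion rather than a laboratory result, no removal of catheter identity is stated, and the receiving committee also acts on the comparison built from these cases. At stake is the credibility of a superiority claim on the primary endpoint.

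**Working it through.** **1. Reproduce the plan's sample size.** Inputs from Study population: 6% and 3%, 80% power, significance level 0.05, 10% dropout, N = 1818. Two-sided tests are stated under Principles and 1:1 allocation under Randomisation.
- Two-proportion formula with continuity correction, alpha 0.05: 814 per arm, so 1628 / 0.90 = 1809.
- The same at the final-look alpha of 0.049002 (Table 2): 819 per arm, so 1638 / 0.90 = 1820.

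Both are close to 1818, so the stated figure stands. Evaluable patients per arm: 1818 × 0.90 / 2 = 818.

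**2. Where knowledge of the arm can enter.**

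| Step | Who acts | Arm known? |
|---|---|---|
| Cultures taken | Scheduled for participants | Not shown to depend on suspicion |
| Organism match or time to positivity | Laboratory result | Little room for judgement |
| Exclusion of another source | Clinicians | Yes for the inserting physician (inferred from Randomisation) |
| Raising a suspected case | Not named; on its face the clinicians | As above |
| Discussion | Chief doctor of the medical group | Not stated |
| Presentation | Data safety monitoring committee | Not stated |

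The exposure is confined to the third and fourth rows, and nothing later in the stated route is said to be masked.

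**3. What differential recognition would do.** Assumptions, none given in the documents: no true effect, 6% true rate in both arms, 818 per arm, final look only, critical value 1.96, and antimicrobial-arm cases recognised at a fraction r of the control-arm rate.

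With p1 = 0.06, p2 = 0.06r and p̄ = (p1 + p2)/2:
- SE0 = √(2p̄(1 − p̄)/818)
- SE1 = √((p1(1 − p1) + p2(1 − p2))/818)
- P(false superiority) = Φ((p1 − p2 − 1.96·SE0)/SE1)

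For r = 0.90: p2 = 0.054, SE0 = 0.011464, SE1 = 0.011463, argument = (0.006 − 0.02247)/0.011463 = −1.437, probability 7.5%.

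For r = 0.80: p2 = 0.048, SE0 = 0.011176, SE1 = 0.011172, argument = (0.012 − 0.02190)/0.011172 = −0.887, probability 18.8%.

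| r | Expected recognised cases (control v antimicrobial) | P(false superiority) |
|---|---|---|
| 1.00 | 49.1 v 49.1 | 2.5% |
| 0.95 | 49.1 v 46.6 | 4.4% |
| 0.90 | 49.1 v 44.2 | 7.5% |
| 0.80 | 49.1 v 39.3 | 18.8% |
| 0.70 | 49.1 v 34.4 | 38.0% |

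Using the Table 2 final bound of 1.96857 instead changes little: 7.4% at r = 0.90 and 18.5% at r = 0.80. With a true rate of 4.5% in both arms and critical value 1.96, these become 6.6% and 15.0%.

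**4. Tipping point in a single data set.** Pooled z at 818 per arm, starting from 37 v 37 (4.5% in each arm, also an assumption):
- 37 v 22 gives z = 1.99 and 37 v 23 gives 1.84. Crossing 1.96857 by loss from one arm alone needs 15 of 37 cases, or 41%.
- 46 v 28 gives z = 2.14 and 45 v 29 gives 1.90. Moving cases both ways needs 9 of 37 in each arm, or 24%.

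**The case against.** The strongest reply is that the endpoint is anchored in cultures. A clinician cannot create a case without them, and the cultures are scheduled whether or not infection is suspected. Referred cases also go to a committee whose members are not investigators. Masked case files and adjudication procedures are the kind of detail an article leaves to its supplement, so their absence here is weak evidence that they do not exist.

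Much of this stands, and it rules out several stronger readings that a reader might infer:
- **That treating clinicians decide the endpoint.** Positive cultures are required, cases reach the committee, and the final decider is not stated.
- **That a case nobody suspects is never reviewed.** The word suspected directly follows the culture definition and the source-exclusion sentence, so it may mean a culture-positive case awaiting source exclusion. The objective components are recorded in any event.
- **That the committee is not independent because its members come from the centres.** The same sentence says they are not investigators, and nothing says that they or the chief doctor see the allocation.
- **That a small shift decides the trial.** From a null starting point, the tipping examples need 24% to 41% of cases to move, which is not small.
- **That the bias favours the product.** This direction is plausible, but nothing in the documents shows it.

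The reply does not dispose of the point. The article itself states who excludes another source, what triggers review and which body receives the cases. Those are stated choices, and they leave the judgement part of the endpoint open to arm-dependent attribution.

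**Conclusion.** The concern holds in a limited form. Exclusion of another source and referral of suspected cases rest with clinicians whose knowledge of the catheter is inferred from the Randomisation section; the article makes no explicit open-label statement. No masked classification of all culture-positive patients is stated, and the committee that receives the cases also advises on stopping.

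The size depends on a recognition deficit that the documents do not give. A 10% relative deficit, about 5 of 49 expected cases, would triple the one-sided error, from 2.5% to about 7.5%; a 20% deficit would bring it to about 19%. A 5% deficit gives 4.4%. These figures illustrate sensitivity and do not predict what will happen. The sample size and Table 2 are not in question. This is a cheap improvement to the stated route, not evidence that the endpoint is invalid.

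**What to change.** In Study endpoints, replace the suspicion trigger with a laboratory one: every participant with a positive peripheral blood culture, or whose paired central and peripheral cultures meet the criterion of more than 120 minutes, goes to review. Reviewing patients with only a positive tip culture would add little, because the tip criterion also needs a positive blood culture.

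Present these cases to the existing committee with catheter type and allocation removed from the file. Classify them by the written criteria, including source exclusion. State that this masked classification is the primary endpoint, and keep the clinicians' classification as a sensitivity analysis.

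Complete the classification of the cases entering each analysis before the committee sees any comparison by arm. For cases arising after the interim look, the redaction is what protects the judgement.

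The cost is redaction work and somewhat more cases to read. The cultures are already scheduled, so no new tests are needed. Splitting the committee, or barring members from cases at their own centre, would depend on a committee size that the article does not give and is not needed for the main gain.

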### Study population

The study sample size is calculated on the basis of an expected CRBSI rate of approximately 6% for the control group and 3% for the antiseptic catheter group. Allowing for a 10% dropout rate, 1818 patients are required to yield a study with 80% power at a statistical significance level of 0.05.

### Participant selection and recruitment

Before identifying and screening patients for eligibility, informed consent (see online supplementary file) must be obtained by the doctor in charge. All information will be transferred into an electronic database so that the trial office can monitor recruitment and refusal rates at each centre.

### Randomisation

Each research centre will receive sequentially numbered containers used to implement the random allocation sequence, and the treatment allocation group will be hidden beyond the coated card. To ensure that patients are randomly assigned at a 1:1 ratio at each study centre, the randomised cards will be protected using a block design (each block includes four random allocation sequences). For a patient who meets the required criteria, the local investigator opens a randomised card that records the screening number and treatment allocation group. Then, the physician in charge of the patient will obtain the correct study catheter and complete catheterisation. Hence treatment allocation will be concealed.

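### A fixed block of four within each centre lets staff who track the sequence deduce up to one third of allocations, which weakens the concealment that the protocol claims

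*Protocol article*

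**What the plan says.** All of this is in the protocol article.

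- **Setting** (Study design): "controlled, randomised clinical trial conducted at 12–16 hospital centres in China".
- **Ratio** (Randomisation): the aim is given as "To ensure that patients are randomly assigned at a 1:1 ratio at each study centre".
- **Blocks** (Randomisation): the method chosen for that aim is that "the randomised cards will be protected using a block design (each block includes four random allocation sequences". No other block size is named.
- **What hides the allocation** (Randomisation): numbered containers are sent to each centre, and "the treatment allocation group will be hidden beyond the coated card".
- **Who learns it** (Randomisation): for an eligible patient, "the local investigator opens a randomised card that records the screening number and treatment allocation group". After that, "the physician in charge of the patient will obtain the correct study catheter and complete catheterisation".
- **Conclusion drawn** (Randomisation): "Hence treatment allocation will be concealed".
- **Room for judgement at entry** (Eligibility criteria): the catheter must be expected to stay in for 5 days or more, and a patient is excluded who has, "in the opinion of the doctor, a situation that is not suitable for indwelling placement".
- **Size** (Study population): 1818 patients.

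**The concern.** Concealment has two parts. The person enrolling must not be able to see the current allocation, and must not be able to work it out from earlier ones. The coated card deals with the first part only. With blocks of known size four and two places per arm, two like allocations at the start of a block fix the other two, and any three fix the fourth. The section's last step, fetching the named catheter after the card is opened, reveals an allocation and does nothing to protect the next one.

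Prediction matters only if someone can act on it, and here there is some room to do so. Whether a catheter will be needed for 5 days, and whether a patient is unsuitable, are partly matters of opinion. A clinician who expects a particular catheter next could, knowingly or not, enrol or pass over a patient according to perceived infection risk. That would unbalance the arms at entry. The primary comparison, as described under Proposed primary analysis, stratifies by the time at which CRBSI occurs and names no adjustment for baseline risk.

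**Working it through.** **Inputs.** Block size 4, ratio 1:1 within centre, and allocations known to local staff once made (Randomisation); 12 to 16 centres (Study design); N = 1818, with CRBSI 6% v 3%, 80% power, 5% significance and 10% dropout (Study population).

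**1. The plan's own figure.** The article gives no predictability figure; 1818 serves here only to turn a share into a count. It can be reproduced closely:

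- Uncorrected size per arm: n' = [z(0.975)·√(2·0.045·0.955) + z(0.80)·√(0.06·0.94 + 0.03·0.97)]² / 0.03² = 749 after rounding up.
- Continuity-corrected: n = (n'/4)·[1 + √(1 + 4/(n'·0.03))]² = 814.
- Total: 1628 / 0.90 = 1809. At the final-look alpha of 0.049 it is 819 per arm, and 1638 / 0.90 = 1820.

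Both totals lie within 0.5% of 1818, so the sample size is not in question here.

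**2. Allocations fixed by earlier ones.** Call the arms A and B. A block with two of each has six equally likely orders:

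| Order | Fixed in advance |
|---|---|
| AABB | 2 (third, fourth) |
| ABAB | 1 (fourth) |
| ABBA | 1 (fourth) |
| BAAB | 1 (fourth) |
| BABA | 1 (fourth) |
| BBAA | 2 (third, fourth) |

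Mean = (2+1+1+1+1+2)/6 = 8/6 = 1.33 per block. Share = 1.33/4 = 33.3%.

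**3. Best-guess accuracy.** Guess the arm with more places left. The chance of being right is 1/2 for the first place, 2/3 for the second, 1/3·1 + 2/3·1/2 = 2/3 for the third, and 1 for the fourth. The sum is 17/6 per block, so accuracy is 17/24 = 70.8%, against 50% by chance.

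**4. As a count.** 1818/3 = 606 expected, slightly fewer if a centre's last block is incomplete. This takes perfect tracking at every centre.

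**5. Effect of other block schemes.** Fixed sizes were enumerated exactly. Mixed sizes were simulated: 400 sequences of 114 allocations (about one centre's share with 16 equal centres, 1818/16 = 113.6). The observer sees every earlier allocation and knows the set of sizes, but not their order.

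| Scheme | Certain in advance | Best guess right |
|---|---|---|
| Fixed 4 | 33.3% | 70.8% |
| Fixed 6 | 25.0% | 68.3% |
| Fixed 8 | 20.0% | 66.6% |
| Mixed 4/6 | 5.4% | 69.2% |
| Mixed 4/6/8 | 2.3% | 67.9% |

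As a check, the same simulation with fixed 4 gave 32.8% and 70.6%, close to the exact values. Under mixed 4/6/8 the certain count is about 0.0234 × 1818 = 43. Varying the size therefore removes most of the certainty but little of the guessability.

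**6. Possible bias: an assumption, not an estimate.** Suppose every centre tracked perfectly and steering produced a difference of δ in baseline CRBSI risk between arms among the determined third only. The overall difference would shift by δ/3. For an assumed δ of 1 to 4 percentage points, that is 0.33 to 1.33 points, or 11% to 44% of the planned 3-point effect. Nothing in the documents fixes δ.

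**The case against.** The case on the other side has several sound parts.

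- **Tracking is assumed.** Certainty requires someone to know the block size, know where each block starts, and hold an ordered record of the centre's allocations. The article shows only that whoever opens a card learns that card. It gives consent to the doctor in charge, card opening to the local investigator and insertion to the physician in charge, and a treating doctor may see only his or her own patients' results. This stands: one third is an upper limit, not a forecast.
- **The card does real work.** It is opened only for a patient who meets the criteria. Participant selection and recruitment puts consent before screening, and has the trial office watch recruitment and refusal rates by centre. These safeguards stand. They do not remove the problem, because foreknowledge comes from earlier cards and not from a premature look at the current one.
- **Discretion is limited.** The 28-day survival criterion applies to patients with malignant disease, and the doctor's-opinion criterion is followed by named conditions. This stands, but the expected catheter duration and the opinion clause still leave some room.
- **The wording is loose.** The text speaks of four sequences per block, not four allocations. Four allocations is the natural reading, but the figures depend on it.

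A reader might infer that allocation is not concealed at all, or that about 600 patients will in fact be enrolled with their arm known. The documents support neither. They describe a system that permits deduction; they do not show that anyone keeps a tally or acts on it.

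**Conclusion.** The point holds as a weakness in concealment. With one fixed block of four per centre, and with local staff learning each allocation, up to one third of allocations (at most about 606 of 1818) can be deduced beforehand, and a best guess is right 71% of the time. The article's inference that allocation is therefore concealed does not follow from the procedure it describes.

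This rests on three assumptions: that a block holds four allocations, that staff know this (the article prints it), and that they follow their centre's sequence. The first is the natural reading, the second is likely, and the third is unknown. The consequence is a risk of selection bias in the CRBSI comparison, whose size and direction cannot be derived from the documents. Sample size, power and alpha are unaffected. The change is worth making because it is cheap; the weakness does not by itself invalidate the trial.

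**What to change.** For cards not yet issued, have the statistician generate each centre's list with block sizes varying at random, for example 4, 6 and 8. The statistician should hold the list and the sizes and disclose neither to sites, and the sizes should be left out of documents that investigators receive. Start each new list at the end of the centre's current block, so that no part-block imbalance is carried over.

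For cards already used, qualify the concealment sentence: the current allocation was hidden, but with a fixed block of four later ones could in part be predicted. The SOFA and APACHE II scores already collected at baseline could also be compared between arms at the predictable places in each block. That check can reveal steering, but it cannot rule out steering on unrecorded factors.

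The change should be described as removing certainty rather than guessability: 33% falls to about 2% even if the set of sizes leaks, but best-guess accuracy falls only from 71% to about 68%. Requiring consent and eligibility before the card is opened would add little, since the plan already sets that order.

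The cost is reprinting unissued cards and a possible within-centre imbalance of up to 4 patients instead of 2.
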